## Safety Assessments

We do an assessment of suicidal ideation and behavior at every assessment time-point as these are our study outcomes. We do not utilize any other safety assessments. If the adolescent endorses suicidal ideation with intent and/or plan within the prior 2 weeks on the C-SSRS, then the RA contacts the clinician who conducts the suicidality procedures described below (See Appendix for full details).

**What is the degree of suicide risk?** Determine the extent of suicidality by asking about ideation, method/plan, the presence of threats (e.g. suicide note) and actual behaviors. If they endorse suicidal ideation, determine the risk that patient will move from low to higher risk. If an attempt has already occurred, determine its nature and assess future risk.

What is your urge to harm yourself right now?

What is your intent to kill yourself right now?

How often do you think about suicide?

How well can you control your thinking about suicide right now?

How well can you control your emotions right now?

How well can you control your actions and behavior right now?

1. **Irrespective of intent, what is preferred method for suicide?** What is the lethality and where will the method occur. i.e., will the person be isolated or is there potential for discovery?
2. **Suicidal intent?** Ask specifically about whether the patient has a desire to die. If yes, consider the degree and type of motivation: actually wants to die, does not particularly want to die but rather wants to escape an intolerable situation or wants to communicate something, such as asking for help, getting attention, making someone feel sorry or change their mind.
3. **Use of alcohol and other drugs**
4. **How effective is the environment for keeping the patient safe?**
5. **Complete safety plan if person will remain in the community.** If assessment indicates an emergency evaluation is necessary, make a plan with the parent and arrangements for an ambulance to transport the youth to the ED.

## Adverse Events and Serious Adverse Events

### Definition of Adverse Events

This protocol uses the definition of adverse event from 21 CFR 312.32 (a): any untoward medical occurrence associated with the use of an intervention in humans, ***whether or not considered intervention-related***. Expected adverse events in this study include NSSI that does not result in hospitalization and breach of confidentiality.

### Definition of Serious Adverse Events

The outcome points for this study include suicidal behavior and hospitalizations/ED visits for suicidal ideation; these have not been considered serious adverse events with suicidal individuals per past IRB guidance. Nonetheless, we will record suicidal behavior and psychiatric ED/inpatient hospitalizations due to suicidal ideation or suicidal behavior as expected SAEs, as well as psychiatric ED visit or inpatient hospitalization not due to SI or a suicide attempt. Given the nature of the population, suicide deaths, although rare in this age group, will also be considered expected SAEs.

The following guidelines will be used to describe severity.

- **Mild** – Events require minimal or no treatment and do not interfere with the participant’s daily activities.
- **Moderate** – Events result in a low level of inconvenience or concern. Moderate events may cause some interference with functioning.
- **Severe** – Events interrupt a participant’s usual daily activity and may require emergency or other treatment. Severe events are usually potentially life-threatening or incapacitating.

#### Relationship to Study INTERVENTION/Experimental Manipulation

All adverse events (AEs) will have their relationship to study procedures, including the intervention, assessed by the project Safety Officer, based on temporal relationship and his/her clinical judgment. The degree of certainty about causality will be graded using the categories below.

- **Definitely Related** – There is clear evidence to suggest a causal relationship, and other possible contributing factors can be ruled out. The clinical event occurs in a plausible time relationship to study procedures administration and cannot be explained by concurrent psychiatric presentation or other factors, such as drugs or chemicals. The response to withdrawal of the study procedures should be clinically plausible. The event must be phenomenologically definitive.
- **Probably Related** – There is evidence to suggest a causal relationship, and the influence of other factors is unlikely. The clinical event occurs within a reasonable time after administration of the study procedures, is unlikely to be attributed to concurrent psychiatric symptoms or other drugs or chemicals, and follows a clinically reasonable response on withdrawal.
- **Potentially Related** – There is some evidence to suggest a causal relationship (e.g., the event occurred within a reasonable time after administration of study procedures). However, other factors may have contributed to the event (e.g., the participant’s clinical condition, other concomitant events). Although an AE may rate only as “possibly related” soon after discovery, it can be flagged as requiring more information and later be upgraded to “probably related” or “definitely related”, as appropriate.
- **Unlikely to be related** – A clinical event whose temporal relationship to study procedures administration makes a causal relationship improbable (e.g., the event did not occur within a reasonable time after administration of the study procedures) and in which other drugs or chemicals or associated psychiatric symptoms provides plausible explanations (e.g., the participant’s clinical condition, other concomitant treatments).
- **Not Related** – The AE is completely independent of study procedures administration, and/or evidence exists that the event is definitely related to another etiology. There must be an alternative, definitive etiology documented by the clinician.

#### Expectedness

The PIs will review every adverse event (AE) and make their own determination regarding whether it is expected or not and related to the study. Our Safety Officer, a clinical psychologist, independent of the study team, with appropriate expertise in suicidal behaviors will be responsible for the ultimate decision of whether an AE is expected or unexpected, and related to the study. An AE will be considered unexpected if the nature, severity, or frequency of the event is not consistent with the risk information previously described for the study procedures.

Given the target recruitment population (adolescents at risk for suicide) and the primary outcomes of suicidal events and ideation, most AEs of this nature will be expected events.

### Time Period and Frequency for Event Assessment and Follow-Up

The occurrence of an adverse event (AE) or serious adverse event (SAE) may come to the attention of study personnel during study visits: baseline, follow-up assessments as well as intervention sessions.

All AEs, will be captured on the appropriate case report form (CRF). Information to be collected includes event description, time of onset, clinician’s assessment of severity and expectedness, relationship to study procedures (assessed only by those with the training and authority to make a diagnosis), and time of resolution/stabilization of the event. All AEs occurring while on study will be documented appropriately regardless of relationship. All AEs will be followed to adequate resolution.

Any medical or psychiatric condition that is present at the time that the participant is screened will be considered as baseline and not reported as an AE.

Changes in the severity of an AE will be documented to allow an assessment of the duration of the event at each level of severity to be performed. Documentation of onset and duration of each episode will be maintained for AEs characterized as intermittent.

Study personnel will record events with start dates occurring any time after informed consent is obtained until 7 (for non-serious AEs) or 30 days (for SAEs) after the last day of study participation. At each study visit, the investigator will inquire about the occurrence of AE/SAEs since the last visit. Events will be followed for outcome information until resolution or stabilization.

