# STUDY INTERVENTION/EXPERIMENTAL MANIPULATION DISCONTINUATION AND PARTICIPANT DISCONTINUATION/WITHDRAWAL

## Discontinuation of Study Intervention/Experimental Manipulation

When a subject discontinues from the study intervention, whether voluntarily or involuntarily, but not from the study, remaining study procedures will be completed as indicated by the study protocol. If a clinically significant finding is identified (including, but not limited to changes from baseline) after enrollment, the investigator or qualified designee will determine if any change in participant management is needed. Any new clinically relevant finding will be reported as an adverse event (AE).

The data to be collected at the time of study intervention discontinuation will include the following:

- The reason(s) for discontinuing the participant from the intervention, and methods for determining the need to discontinue
- If the participant is due to complete assessments within 2 weeks of being discontinued from the study intervention, those assessments will be administered at the time of discontinuation; if the next scheduled assessments are more than 2 weeks from the discontinuation date, the discontinued participant will wait for the next scheduled assessment. Thereafter, the participant will be included in all future scheduled assessments, even though not participating in the intervention.

A participant may be involuntarily discontinued from the study intervention if the participant has an unexpected adverse reaction to intervention content, develops psychiatric symptoms that make continuation of the intervention impossible, or if clinical staff deem it is not clinically appropriate to continue the intervention during the psychiatric admission. The participant will also no longer receive the messages, if they are discontinued from the study.

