### Adverse Event Reporting

Once staff members report an AE to MPIs, Drs. [name] or [name] will code severity, causal relationship, and whether the event was expected. If necessary, they will seek further information from the participant or parent or other source before coding. AEs will be coded on a weekly basis.

Any potential SAE will be internally reviewed (typically within 24 hours) by one of the MPIs (or a qualified designee in their absence) and independently will be reviewed by the Safety Officer at the same time. Coding of AEs and SAEs occurs on a study AE case report form. In the case of disagreement, the PIs and SO will discuss, but the SO’s determination will be adopted.

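### Section 8.3.3 treats every condition present at screening as baseline with no exception for worsening, so deterioration short of an SAE may go unrecorded as an AE

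*Protocol*

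**What the plan says.** Section 8.3.3 (Time Period and Frequency for Event Assessment and Follow-Up) fixes what staff leave out, for medical and psychiatric illness alike: a "condition that is present at the time that the participant is screened will be considered as baseline and not reported as an AE". The section then says that "Changes in the severity of an AE will be documented". It sets the recording window as "Study personnel will record events with start dates occurring any time after informed consent is obtained", up to 7 or 30 days after the last day of participation. It adds that "Documentation of onset and duration of each episode will be maintained for AEs characterized as intermittent".

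Section 7.1 (Discontinuation of Study Intervention) provides for a management decision when "a clinically significant finding is identified (including, but not limited to changes from baseline) after enrollment". Its reporting sentence reads "Any new clinically relevant finding will be reported as an adverse event (AE").

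On review, section 8.3.2 says "All adverse events (AEs) will have their relationship to study procedures, including the intervention, assessed by the project Safety Officer", and its Expectedness part gives the Safety Officer the final decision on expectedness. Section 8.3.4 begins the coding by the principal investigators "Once staff members report an AE to MPIs".

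**The concern.** Adolescents enter this trial because they are already ill. Inclusion criterion 5 requires a suicide attempt or ideation within the past month, and the Background expects mood disorders in most participants. The conditions that 8.3.3 sets aside as baseline are therefore the ones most likely to deteriorate during follow-up.

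Section 8.3.2 records suicidal behavior and psychiatric ED visits or admissions as expected SAEs whatever the baseline state. Below that level nothing equivalent exists. A staff member who follows 8.3.3 as written could decline to report a marked worsening of depression, or of ideation that never remitted, because the condition was there at screening. The AE route would then not start for that event: no coding by the investigators, no relatedness or expectedness ruling by the Safety Officer, and no entry in the annual AE report to the DSMB.

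**Working it through.** The protocol states no figure on this point, so the check sets its texts side by side and asks whether any of them restores worsening.

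1. **8.3.3, baseline rule.** This is an instruction not to report. It has no clause on later change.
2. **8.3.3, severity sentence** ("Changes in the severity of an AE will be documented"). It applies to something already recorded as an AE. A condition classed as baseline is not one, so its worsening is not covered.
3. **8.3.3, recording window** ("Study personnel will record events with start dates occurring any time after informed consent is obtained"). It depends on a start date. Worsening of continuous depression or ideation may have no start date after consent. A new, separate episode does have one, so the window supports recording that.
4. **8.3.3, intermittent events** ("Documentation of onset and duration of each episode will be maintained for AEs characterized as intermittent"). Again this applies to AEs only. It helps with episodic events, not with continuous ones.
5. **8.3.1, AE definition.** It is wide enough to take in deterioration, related or not. The expected AEs that it names are non-suicidal self-injury without hospitalization and breach of confidentiality. Worsening depression and ideation are not named.
6. **2.3.1 and the Expectedness part of 8.3.2.** The first lists later suicidal ideation among possible adverse events. The second supposes that AEs of this kind will occur and will mostly be expected. Since every participant enters with a recent attempt or ideation, the authors evidently did not regard presence at screening as a complete bar. Neither text says that worsening of a baseline condition counts.
7. **7.1.** Changes from baseline fall within its trigger, but the trigger leads to a management decision. The AE sentence is limited to a *new* finding, and it stands under intervention discontinuation.

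Items 5 to 7 point toward recording worsening, while item 1 points against it and is the more specific instruction. No text resolves the conflict.

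**Reach of the rule.** The Background gives mood disorders in 92% of the earlier STEP samples and anticipates the same features here. With the target of 216 participants:

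0.92 × 216 = 198.7, about 199 participants

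This is the number to whom the baseline rule would apply for a mood disorder. It is neither the number expected to worsen nor a count of lost AEs. Going further would need a rate of worsening short of suicidal behavior, an ED visit or an admission, and the protocol gives none.

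**The case against.** The strongest reply is that 8.3.3 excludes only the state of a condition at screening and is silent on later change, so that the general definition in 8.3.1 governs deterioration. On this view *new* in 7.1 means newly identified after enrollment and takes in the changes from baseline named in the same paragraph. That reading is possible and probably closer to what the authors intended. It does not remove the point: a do-not-report rule that must be read against its literal wording is badly fixed, and staff make the first decision before any central coding.

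The reply is fully right about consequence. A reader might infer that worsening left off the AE form can never get a relatedness judgment. The protocol does not support that. Section 8.3.2 says that all AEs are assessed, not that only AEs are. Section 8.4 provides a separate route: an incident or outcome that is unexpected, possibly related and suggestive of greater risk is an Unanticipated Problem, reviewed by the investigators and the Safety Officer, and need not be an AE. What can still slip through is worsening that fails one of those three tests.

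Nor is deterioration invisible. BDI-II depression and active ideation are primary outcomes. Ideation with intent or plan in the prior 2 weeks triggers clinician contact (8.2). Section 2.3.1 provides for contact with the patient's own clinician on clinical deterioration. The Safety Officer sees aggregate safety and efficacy data by arm (10.1.6). These measures do not produce an event-level AE record, but they limit the harm.

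A reader might also infer that self-injury and new episodes of ideation are shut out. The texts in items 3 to 6 of the working support recording them, so for these there is tension rather than exclusion.

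**Conclusion.** The point holds as a minor defect in the safety wording. Section 8.3.3 gives an unqualified instruction not to report conditions present at screening, and no other section clearly restores clinically significant worsening. Read literally, worsening of existing depression or continuous ideation below the SAE level need not be recorded as an AE and may miss the routine relatedness and expectedness review.

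The effect is limited to the AE record. No estimate, test or endpoint changes. Its size is unknown; the figure of about 199 shows only how widely the rule applies, and it assumes that the 92% of the earlier samples carries over. The conclusion rests on staff applying 8.3.3 as written. If they already record worsening by custom, little is lost, and the fix simply brings the text into line.

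**What to change.** Add one sentence to 8.3.3 after the baseline rule: *Clinically significant worsening, in the investigator's judgment, of a condition present at screening that occurs after consent will be recorded as an AE.* In 7.1, insert *or worsened* after *new* in the AE sentence, so that the two sections agree.

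Do not add a rule that each episode of ideation is an AE. That goes beyond the gap and would duplicate an outcome already rated week by week under section 8.1.

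The change needs no new assessments. The price is somewhat more AE forms and a higher AE count. The threshold is left to the investigator, so some variation between raters will remain, limited by the weekly central coding in 8.3.4.

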### Adverse Event Reporting

Once staff members report an AE to MPIs, Drs. [name] or [name] will code severity, causal relationship, and whether the event was expected. If necessary, they will seek further information from the participant or parent or other source before coding. AEs will be coded on a weekly basis.

Any potential SAE will be internally reviewed (typically within 24 hours) by one of the MPIs (or a qualified designee in their absence) and independently will be reviewed by the Safety Officer at the same time. Coding of AEs and SAEs occurs on a study AE case report form. In the case of disagreement, the PIs and SO will discuss, but the SO’s determination will be adopted.

### Serious Adverse Event Reporting

As noted above, in addition to the review by the MPIs, the independent Safety Officer will be responsible for conducting an evaluation of serious adverse events. SAE reports will be provided to the IRB and NIMH DSMB according to the timelines listed in Table 1. SAEs that are unanticipated, serious, and possibly related to the study intervention will be reported on an expedited timeline (5 business days) to the DSMB and IRB, in accordance with requirements. Deaths (by suicide or other causes) will be reported within 5 days to the IRB and NIMH DSMB.

Expected or unrelated SAEs will be reported in a less urgent manner to the IRB and the NIMH DSMB on the reporting timeline included in Table 1; AEs will be reported to the NIMH DSMB on an annual basis.

## Unanticipated Problems

### Definition of Unanticipated Problems

This protocol uses the definition of Unanticipated Problems as defined by the Office for Human Research Protections (OHRP). OHRP considers unanticipated problems involving risks to participants or others to include, in general, any incident, experience, or outcome that meets **all** of the following criteria:

- Unexpected in terms of nature, severity, or frequency given (a) the research procedures that are described in the protocol-related documents, such as the Institutional Review Board (IRB)-approved research protocol and informed consent document; and (b) the characteristics of the participant population being studied;
- Related or possibly related to participation in the research (“possibly related” means there is a reasonable possibility that the incident, experience, or outcome may have been caused by the procedures involved in the research); and
- Suggests that the research places participants or others at a greater risk of harm (including physical, psychological, economic, or social harm) than was previously known or recognized.

### Unanticipated Problems Reporting

The investigators and Safety Officer will review all unanticipated problems (UPs) and report them to the reviewing IRB and to the DSMB. The UP report will include the following information:

- Protocol identifying information: protocol title and number, PI’s name, and the IRB project number
- A detailed description of the event, incident, experience, or outcome
- An explanation of the basis for determining that the event, incident, experience, or outcome represents an UP
- A description of any changes to the protocol or other corrective actions that have been taken or are proposed in response to the UP

To satisfy the requirement for prompt reporting, UPs will be reported using the following timeline:

- UPs that are serious adverse events (SAEs) will be reported to the IRB and DSMB, and to the study sponsor/funding agency within 5 working day of the investigators becoming aware of the event.
- Any other UP will be reported to the IRB and DSMB within 5 business days of the investigator becoming aware of the problem and reviewing with the Safety Officer.
- All UPs should be reported to appropriate institutional officials (as required by an institution’s written reporting procedures), NIMH, and the Office for Human Research Protections (OHRP) within 5 days of the IRB’s receipt of the report of the problem from the investigator.

*See* ***CD Section 8.4.1*** *for additional example text applicable for devices.*

# STATISTICAL CONSIDERATIONS

**Data Analyses.** In this section, we describe aim by aim the proposed method of data analysis and sample size considerations. **Scientific rigor** is enhanced and maintained by: 1) randomization procedures, 2) having assessment staff blind to condition, 3) multiple modalities of assessment, 4) comprehensive retention procedures, 5) preliminary analyses, 6) missing data procedures, and 7) data analytic strategies that are consistent with best practices for the analysis of randomized clinical trials as embodied in the Consolidated Standards of Reporting Trials (CONSORT) statement (75)**.** Additionally, relevant biological variables, specifically sex, are considered in the experimental design. We do not have a priori hypotheses regarding sex differences in the effect of STEP on our study outcomes. Accordingly, and in agreement with NIH guidance on this topic our plan is to separately tabulate results by sex but test our main hypotheses in a sample with both sexes combined (<http://orwh.od.nih.gov/sexinscience/overview/pdf/NOT-OD-15-102_Guidance.pdf>). Finally, by collecting implementation outcome data, we will be able to identify and develop implementation strategies to encourage greater uptake and adoption of STEP in a future R01 implementation trial. As all our hypotheses are pre-specified, no adjustment for multiplicity will be used.

[figure not shown]
Our randomization procedures include stratification on important predictors of the main outcome variable and are automated and protected from inadvertently revealing treatment assignment order to staff. This will help ensure the blinding of assessment staff to treatment condition. Our plan for how missing data will be

handled with multiple imputations, with assumptions checked with sensitivity analyses (76), is pre-specified (as are all aspects of our analysis plan). We will adhere to intent-to-treat principles, and all aspects of data analysis will be pre-specified as reflected in this proposal, and with modification following proposal review and discussions with program and our Data Safety and Monitoring Board. Preliminary analyses will include descriptive statistics to examine the distributional and psychometric properties of the variables (e.g., normality, internal consistency). Variables will be transformed to better approximate normality if this is necessary given the observed distribution and the assumptions of the analysis model. We will also examine post-inclusion attrition by comparing study completers to dropouts on sociodemographic, baseline data, and psychotropic medication usage to determine if they differ systematically. We will examine the success of the stratified randomization by examining between-group differences at baseline. Preliminary analyses may also include analyses of adverse events, the progress of recruitment and retention, and data processing and quality markers as the study progresses. Daily mood monitoring data is not included in outcome analyses because it is conceptualized as part of this adjunctive intervention and only collected in one condition.

Missing data. To accommodate attrition and other sources of missingness, we will utilize the method of multiple imputation by chained equations. At least 50 replicates of each missing value will be generated for inclusion in analyses. This method can accommodate clustering of repeated measures at the level of the. We have previously used these methods in successful analyses of trials of exercise interventions.

Statistical computing. Modeling will be performed using Stata (Stata Corp, College Station, TX, version 16.2 or higher) and R software (R Foundation for Statistical Computing, Vienna, Austria, version 4.0 or higher) and Mplus (version 8.4 or higher, Muthen & Muthen, Los Angeles, CA). Analyses and reporting will be executed and archived to ensure full replicability and reproducibility by analysts at Brown University, under the direction of the project methodologist, [name].

**Aim 1A-C:** *Examine the effectiveness of STEP in reducing suicidal events, active SI*, *and depression at 3- and 6-month follow-up (f/u).* We hypothesize that those randomized to STEP, compared to ETAU, will have (**H1A**) lower prevalence of suicidal events (operationalized as either a suicide attempt or emergency intervention to intercede when there is a high likelihood of an attempt) **(H1B**) lower prevalence of time with active SI (operationalized as SI with intent or plan), and (**H1C**) lower level of depressive symptoms, over the 6-month follow-up period. Aim 1 analyses will use a repeated measures design and a multilevel or mixed effect modeling framework. For H1A and H1B, the outcome is binary and a mixed effect logistic regression model will be used. For H1C, the outcome is continuous and a mixed effect general linear model will be used. For H1B, the outcomes are repeatedly observed over follow-up weeks within the 6M timeframe (24 weeks), and can yield a categorical (active SI, worst week) outcome, which would be analyzed like H1A or a continuous (proportion of weeks with active SI) outcome, which would be analyzed differently like H1C. For H1A and H1C the outcome is observed twice at the scheduled follow-ups (3M, 6M). For all hypotheses, we will treat the individual as the random effect. Treatment effects will be estimated as the weighted average of the differences between ETAU and STEP groups over all follow-up times, adjusting for follow-up time.

In secondary analyses to identify potential mechanisms (i.e. mediators) of treatment effectiveness that occur after randomization, we will repeat these analyses using medication use and psychosocial treatment as covariates.

In secondary analyses, payor data will be examined as a potential moderator or predictor of these outcomes.

In secondary analyses, the patterns of change in depressed mood (BDI scores) will be evaluated using random effects models for longitudinal data.

***Sample size and statistical power considerations:*** We determined minimal detectable effect sizes using Monte Carlo methods. This involved generating 1,001 simulated data sets representing our hypothesized effects, and our assumptions of a 10% loss by 3M and another 10% loss by 6M follow-up. We assumed repeated measures of depressive symptoms and the propensity to active suicidal ideation and suicidal events were all correlated at *r* = .5. Across the simulated data sets, we compute power as the proportion of replicates returning a significant effect in the hypothesized direction. Results of these models are summarized in Table 3, above. We summarize effects in terms of Cohen’s effect size statistics for clear expression of the minimum detectable effects. For H1A, H1B, and H1C, we will have sufficient power to detect small-to-medium effect sizes (.46, .31, .35, respectively).

**Aim 1D:** *Examine the effectiveness of STEP in reducing suicidal events at the 12-month f/u.* We hypothesize that those randomized to STEP, compared to ETAU, will have lower rates of suicidal events at the 12-month, long term f/u. This hypothesis will be tested to evaluate the durability of STEP effects over long-term follow-up. We expect to see the full effect of STEP at the 6M follow-up. This hypothesis will be evaluated with logistic regression, and not as part of the repeated measures analysis specified in H1A. If the effect continues through 12M, we will have 80% power to detect a difference in event rates of 38% ETAU and 17% STEP at the 12M follow-up.

In secondary analyses, the within-person frequency of suicidal events and suicidal ideation will be analyzed. These analyses will use (zero inflated) negative binomial regression models to account for the anticipated extreme skew of these outcomes.

***Sample size and statistical power considerations***. The power to test the difference between two proportions, .17 and .38, is significantly different from zero can be found from POWER = F(sqrt(((n*(p1-p2)^2)/(p0*(1-p0)))/2) – F’(1-(a/2))), where F is the cumulative normal density function and F’ is the normal quantile function, a is the desired type-I error level, n is the per-group sample size and p1 and p2 are the target proportions. H1A and H1D have similar minimum detectable effect sizes because we use a conservative estimate of the within-person correlation of propensity to suicide for aims H1A-H1C. We conservatively use 162 as our sample size for these calculations but we expect to have a larger sample with suicidal event data because these data can be drawn from the electronic health record in addition to participant self-report.

**Aim 2:** *Examine engagement of the hypothesized mechanisms at the 3- and 6-month f/u.* We hypothesize that those randomized to STEP, compared to ETAU, will have*:* **H2A:** higher attention to positive affect, assessed by implicit tasks; **H2B**: Increased gratitude and satisfaction with life, assessed by self-report; **H2C**: lower attention to negative affect, assessed by implicit tasks and self-report. Aim 2 analyses will use a repeated measures design and a multilevel or mixed effect modeling framework. For H2A, H2B, and H2C, the outcomes are continuous and a mixed effect general linear model will be used. Outcomes are repeatedly observed over follow-up and assessed at the scheduled follow-up (3M, 6M). For all hypotheses, we will treat the individual as the random effect. Treatment effects will be estimated as the weighted average of the differences between ETAU and STEP groups overall follow-up times, adjusting for follow-up time. ***Sample size and statistical power considerations***: As with H1, we determined minimal detectable effect sizes using Monte Carlo methods. This involved generating 1,001 simulated data sets representing our hypothesized effects, and our assumptions of a 10% loss by 3M and another 10% loss by 6M follow-up. We assumed repeated measures of the measures assessing the mechanisms (attention to positive affect, gratitude and satisfaction with life, and attention to negative affect) to have a stronger correlation within a respondent over time than the Aim 1 outcomes, and assumed *r* = .75, which results in a smaller effective sample size. Across the simulated data sets, we compute power as the proportion of replicates returning a significant effect in the hypothesized direction. Results of these models are summarized in Table 3, above. We summarize effects in terms of Cohen’s effect size statistics for clear expression of the minimum detectable effects. For Aim 2 outcomes, we will have sufficient power to detect small-to-medium effect sizes (*d* = .39).

**Aim 3**: *Examine whether hypothesized mechanisms mediate reduction of suicidal events and ideation*. **H3:** Treatment-related changes in attention to positive affect, gratitude, satisfaction with life, and attention to negative affect at 3M follow-up will be related to improvements in SE and SI at the 6M f/u. Analysis: Mediation will occur when the outcomes (SE, SI) and the putative mediators (PA, gratitude and satisfaction with life, NA) are correlated, and that the distribution of the mediators varies according to treatment (Aim 2). We will approach the analysis using the Baron & Kenney (77) approach to mediation, with modifications for non-normal dependent variables, which is similar to the principal stratification approach to causal mediation analysis (78). We will approach this analysis using a cross-lagged panel model and a path analysis framework. Specifically, we will regress 6M outcomes and mediators on 3M outcomes and 3M mediators, and evaluate the effect of 6M outcomes regressed on 3M mediators accounting for any residual correlation of 6M outcome and 6M mediators and the 3M correlation of outcomes and mediators. All outcomes and mediators at all time points are regressed on treatment condition. We will quantify the total effect of treatment assignment in 6M outcomes, and the indirect effect of treatment in 6M outcomes via M3 mediators. Following Mandolando and Greenland (79), we will infer meaningful level of mediation if at least 10% of the total effect of treatment in 6M outcomes is mediated via M3 mediators. We will characterize the precision and statistical significance of mediation effects using bootstrap methods for interval estimation (80). ***Sample size and statistical power considerations.*** We used Monte Carlo methods to identify conditions in which a 10% difference (or greater difference) in the main treatment effect is to be detected when comparing to a model adjusting for the putative mediator. Finding a mediation effect requires that the treatment group have a different distribution on the putative mediator (attention to positive affect, gratitude and satisfaction with life, attention to negative affect) and the mediator be related to the outcomes (SE, active SI). In plausible scenarios (a unit standard deviation difference on the mediator across treatment group), and a (polyserial) correlation of 0.3 or greater between the mediator and the outcome, we will have adequate (at least 88%) power to detect a 10% mediated effect of treatment group and the outcome (n = 162, 81 per group). Similarly, if the treatment produces a net half standard deviation difference in the mediator (reflecting a clinically meaningful change), and the mediator has a (polyserial) correlation of at least .25 with the outcome, we will have 83% power to detect the target mediated effect.
